# Do β-adrenoreceptor blocking drugs associate with reduced risk of symptomatic osteoarthritis and total joint replacement in the general population? A primary care-based, prospective cohort study using the Clinical Practice Research Datalink

**DOI:** 10.1136/bmjopen-2019-032050

**Published:** 2019-08-01

**Keywords:** osteoarthritis, pain, total joint replacement, anti-hypertensives, analgesia

## Abstract

**Introduction:**

To investigate if β-adrenoreceptor blocking drug (β-blocker) prescription reduces the risk of knee or hip osteoarthritis, total joint replacement and analgesic prescription.

**Setting:**

Primary care.

**Methods and analysis:**

This is a cohort study using data from the Clinical Practice Research Datalink. Two separate analyses will be performed. Study 1 will be on the association between β-blocker prescription and incident knee/hip osteoarthritis. Inclusion criteria will be age ≥40 years. Exposed participants will be those with ≥2 continuous β-blocker prescriptions, and the index date will be the date of the first prescription of β-blocker. Unexposed participants will include up to four controls matched for age, sex, general practice surgery and propensity score for β-blocker prescription. Exclusion criteria will include contraindications to β-blockers, consultations for osteoarthritis or potent analgesic prescription before the index date. Outcomes will be knee osteoarthritis (primary outcome), hip osteoarthritis, knee pain and hip pain. Study 2 will be on the association between β-blocker prescription and total joint replacement and analgesic prescription in people with osteoarthritis. Inclusion criteria will be age ≥40 years, knee or hip osteoarthritis, and index date will be as in study 1. Unexposed participants will be as in study 1, additionally matched for consultation for knee or hip osteoarthritis prior to the index date. Exclusion criteria will include contraindications to β-blockers and osteoarthritis in other joints prior to the index date. Outcomes will be total knee replacement (primary outcome), total hip replacement and new analgesic prescription.

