##### Inclusion criteria

###### Exposed

≥2 continuous prescriptions of β-adrenoreceptor blocking drugs defined as two consecutive prescriptions ≤60 days apart.Age ≥40 years on the date of the first of the two consecutive β-adrenoreceptor blocking drug prescriptions.

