##### Propensity for β-adrenoreceptor blocking drug prescription

As participants prescribed β-adrenoreceptor blocking drugs are likely to have comorbidities, be older and have a high body mass index (BMI), a propensity score for β-adrenoreceptor blocking drug prescription will be calculated using a cumulative logit regression model and including demographic factors and relevant diagnoses at any time prior to β-adrenoreceptor blocking drug prescription (box 1).

Box 1List of potential variables to be included in the calculation of propensity score for β-adrenoreceptor prescriptionDemographic factors.Body mass index (WHO classification categories)*, smoking status* and deprivation score (general practice-level Index of Multiple Deprivation Score).Comorbidities.Hypertension, angina, myocardial infarction, congestive cardiac failure, atrial fibrillation, stroke, high cholesterol, chronic kidney disease, diabetes, anxiety, migraine, Charlson Comorbidity Index (excluding comorbidities in the propensity score) and duration in years of cardiovascular comorbidities prior to cohort entry.Drug prescriptions.Calcium channel blockers, ACE inhibitors, angiotensin II receptor antagonists, bendroflumethiazide, aldosterone antagonists, loop diuretics, alfa-adrenoreceptor blocking drugs, nitrates, nicorandil, aspirin, clopidogrel, statin, fibrate, vitamin K antagonists and non-steroidal anti-inflammatory drugs (in the progression cohort), and as a marker of severity of underlying disease at cohort entry the number of antihypertensive, antiarrhythmic or antianginal drugs prescribed in the 12-month period prior to cohort entry.*Categorised as missing if not available.

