##### Exclusion criteria

Exclusion criteria will be consultation for any of the following prior to the index date:

Osteoarthritis at any joint.Knee, hip, neck or back pain.Conditions causing joint damage or chronic pain: autoimmune inflammatory rheumatic diseases, such as rheumatoid arthritis, psoriatic arthritis, ankylosing spondylitis, lupus, polymyalgia rheumatica, gout, radiculopathy, neuropathy and fibromyalgia.Contraindications to prescription of β-adrenoreceptor blocking medicines: chronic obstructive pulmonary disease, asthma, peripheral vascular disease, heart block, aortic stenosis and hypertrophic obstructive cardiomyopathy.Two consecutive prescriptions for any opioid, any NSAID, gabapentin, pregabalin, duloxetine or amitriptyline prior to the index date.<1 year up-to-standard registration prior to index date to reduce the risk of prevalent cases (eg, with osteoarthritis) being classified as incident cases.^28^

The cohort entry date will be the index date. The unexposed participants will be allocated the index date of their matched exposed participant.

The cohort exit date will be the earliest of the date of the last prescription of β-adrenoreceptor blocking drug prescription, plus 4 weeks or a matched pseudo-exit date for the matched controls, date of the first outcome, date of death, transfer-out date, date of the last data collection or study end date (31 December 2017).

#### Cohort study 2

Cohort study 2 will be on β-adrenoreceptor blocking drug prescription and total joint replacement and analgesic use. The exposure will be as in cohort study 1.

The outcome will be total knee replacement (primary), total hip replacement and analgesic prescription: (1) NSAIDs, (2) opioids, (3) gabapentin or pregabalin, and (4) amitriptyline.

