##### Inclusion criteria

###### Exposed

As in cohort study 1 above.Consultation for knee or hip osteoarthritis prior to the first of the two prescriptions for β-adrenoreceptor blocking drugs.

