##### Exclusion criteria

Exclusion criteria will be previous consultation for any of the following prior to the first prescription of β-adrenoreceptor blocking drug:

Osteoarthritis at any other joint.Neck or back pain.Conditions associated with joint damage or chronic pain (as above).Conditions contraindicating prescription of β-adrenoreceptor blocking medicines (as above).Previous knee or hip replacement.Knee or hip joint replacement within 3 months of the date of the first β-adrenoreceptor blocking drug prescription or matched index date in the unexposed participants. These will be excluded because we do not expect β-adrenoreceptor blocking drug prescription to reduce total joint replacement rates immediately and may be commenced during preanaesthetic check-up.<1 year up-to-standard registration prior to the first qualifying prescription of β-adrenoreceptor blocking drug.^28^
Additionally, participants who receive two consecutive prescriptions for opioids, NSAIDs, gabapentin, pregabalin, duloxetine or amitriptyline prior to the index date will be excluded from the cohort when examining the association between β-adrenoreceptor blocking drug prescription and new analgesic prescription.

The cohort entry and exit dates will be as in cohort study 1. Nearest neighbour matching (±0.2 SD) will be used to match exposed to unexposed participants.

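### The index date is worded so that it can fall on two different dates, and no criterion excludes earlier β-blocker use

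*Protocol article*

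**What the plan says.** The only explicit definition of the index date is in the abstract (Methods and analysis): "the index date will be the date of the first prescription of β-blocker". The body starts follow-up on the index date and gives it to the matched controls (Cohort study 1, Exclusion criteria; Statistical analysis), but does not define it again.

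The body anchors the individual criteria as follows:

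- Exposure (Cohort study 1, Exposed): "≥2 continuous prescriptions of β-adrenoreceptor blocking drugs defined as two consecutive prescriptions ≤60 days apart".
- Age (same section): "Age ≥40 years on the date of the first of the two consecutive β-adrenoreceptor blocking drug prescriptions".
- Osteoarthritis in Study 2 (Cohort study 2, Exposed): "Consultation for knee or hip osteoarthritis prior to the first of the two prescriptions for β-adrenoreceptor blocking drugs".
- Study 2 exclusions: "previous consultation for any of the following prior to the first prescription of β-adrenoreceptor blocking drug".
- Registration in Study 2, within that same list: "<1 year up-to-standard registration prior to the first qualifying prescription of β-adrenoreceptor blocking drug".
- Registration in Study 1: "<1 year up-to-standard registration prior to index date to reduce the risk of prevalent cases (eg, with osteoarthritis) being classified as incident cases".

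Box 1 puts into the propensity score, as a severity marker, "the number of antihypertensive, antiarrhythmic or antianginal drugs prescribed in the 12-month period prior to cohort entry". β-blockers are not left out of that count.

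No inclusion or exclusion criterion in either study mentions β-blocker use before the qualifying pair.

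**The concern.** The index date governs eligibility, the exclusions, the propensity score, the start of follow-up and the controls' dates in both studies. Exposure needs two prescriptions within 60 days, so one earlier isolated issue, or earlier issues more than 60 days apart, separates the first recorded prescription from the first of the pair. Two programmers could each follow the text and build different cohorts.

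Each reading has its own problem. With the first recorded prescription as time zero, the interval up to the qualifying pair is exposed follow-up without continuous treatment. The exit rule does not remove it, because follow-up ends 4 weeks after the last prescription and nothing is said about gaps. With the first of the pair as time zero, people who have already used the drug are analysed as starters. Exclusions such as earlier joint pain or analgesic use, and the score covariates, may then have been affected by that earlier use, and the Box 1 count may include the exposure itself.

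**Working it through.** **1. How many dates the wordings give.**

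| Place | Anchor | Date |
|---|---|---|
| Abstract, index date | first prescription | A on its face; B if read as shorthand |
| Cohort study 1, age | first of the two consecutive prescriptions | B |
| Cohort study 2, prior osteoarthritis | first of the two prescriptions | B |
| Cohort study 2, opening of the exclusions | first prescription | A on its face; B if read as shorthand |
| Cohort study 2, registration | first qualifying prescription | B |

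A is the first β-blocker prescription in the record. B is the first prescription of the qualifying pair. There are three wordings but two dates, because the first of the two and the first qualifying prescription coincide. A and B are the same date unless an earlier issue fails to form a pair.

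**2. Does the registration rule give a β-blocker-free year?**

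- Reading A, Study 1: yes. A first recorded prescription preceded by at least 1 year of registration implies a year without a recorded β-blocker.
- Reading A, Study 2: not guaranteed, because the year is tied to the qualifying prescription and an isolated earlier issue could fall inside it.
- Reading B, both studies: no. Continuous users at registration would usually form their first pair within the first year and be excluded, provided that the first such pair is the one used. Intermittent users, and those with issues more than 60 days apart, can still enter.

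**3. The plan's own figures.** Schoenfeld's formula with two-sided α 0.01, power 0.80, exposed share 0.2 and HR 0.70 gives (2.576 + 0.842)² / (0.2 × 0.8 × (ln 0.70)²) = 573.8 events. Dividing by the stated incidences gives 573.8/0.0065 = 88 273, 573.8/0.0021 = 273 225 and 573.8/0.009 = 63 752. The plan states 88 273, 273 225 and 63 753. The planned sizes are reproduced and do not depend on the index date.

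**4. Possible dilution under reading A.** The documents do not give the untreated share f of exposed follow-up. Assume that a share s of the exposed have an earlier isolated issue, with a gap of g years before the pair and T treated years each. Then f = s·g/(s·g + T). If untreated time carries the unexposed hazard, the HR seen is 0.70(1 − f) + f. The last column is power at 574 events.

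| s | g | T | f | HR seen | Power |
|---|---|---|---|---|---|
| 0.05 | 3 | 10 | 0.15/10.15 = 1.5% | 0.704 | 78% |
| 0.05 | 3 | 5 | 0.15/5.15 = 2.9% | 0.709 | 76% |
| 0.20 | 5 | 10 | 1/11 = 9.1% | 0.727 | 68% |
| 0.20 | 5 | 5 | 1/6 = 16.7% | 0.750 | 57% |

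All values of s, g and T are assumptions. The Sample size section says that over two-thirds of users are treated for more than 10 years, which favours the rows with T = 10.

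**5. Reading B.** The documents give no number of earlier intermittent users and no effect of earlier use on the covariates, so neither the size nor the direction of the bias can be calculated.

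**The case against.** The strongest reply is that the abstract's sentence comes directly after the rule of two or more continuous prescriptions, so that its first prescription means the first of those. On that view the article has one date, the first of the pair, in looser words. This is the more natural reading and it stands. It does not settle the matter, because it is the reading under which earlier users enter as starters, and no criterion stops them.

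A second reply is that few people would be affected. The Statistical analysis section gives 4 weeks as the usual length of a UK prescription, so issues more than 60 days apart need not be common, and the Box 1 problem touches only those with a non-qualifying issue in the previous 12 months. This also stands, and it limits the likely size.

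A third reply is that a condensed article may leave the operational definition to the full protocol. That would cover a missing detail. Here, however, the article itself states anchors that differ.

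A reader might go further and infer that Study 2 counts time before osteoarthritis, nearly free of joint replacement, as exposed follow-up, which would bias towards the hypothesis. The documents do not support this. It needs the abstract's date on its literal reading combined with the body's pair-based osteoarthritis criterion. Against it, the abstract matches controls on an osteoarthritis consultation before the index date, the Cohort study 2 section on unexposed participants says that this matching is to the exposed, and the Study 2 score counts analgesics between the first osteoarthritis consultation and the β-blocker, which presumes that osteoarthritis comes first. Follow-up before age 40 is a similar inference, and it sets aside the abstract's own age criterion.

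**Conclusion.** The index date is not anchored consistently, and earlier β-blocker use is not addressed. As written, the plan either counts some untreated time as exposed or admits earlier intermittent users as new starters. The second is more likely, because the first of the pair is the more natural reading.

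The size cannot be computed from the documents. Under the first-recorded reading, and only if 1.5–17% of exposed follow-up is untreated, an HR of 0.70 would be seen as about 0.70–0.75. The upper end needs one exposed person in five to have an isolated issue 5 years before the pair and only 5 treated years. Under the first-of-pair reading no figure can be given.

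It would also be too strong to say that exposed people never need a β-blocker-free record: in Study 1, the first-recorded reading with the registration rule already implies one year. The point should be fixed before the cohorts are built, but it does not by itself invalidate either study.

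**What to change.** State one index date for both studies: the first prescription of the first qualifying pair, with no β-blocker recorded before it and at least 1 year of up-to-standard registration before it. Anchor to that date the age criterion, the prior osteoarthritis consultation, all exclusions, the propensity score, the 3-month joint replacement rule and the start of follow-up. Controls take the same date from their matched exposed participant.

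Reword the abstract, the inclusion criteria for the exposed in both cohort studies and the exclusion criteria in both to match. Leave β-blockers out of the Box 1 count of drugs in the previous 12 months.

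The cost is some rewording and one programming rule. People with an earlier isolated or widely spaced prescription leave the exposed group. Their number is not given in the documents, so it should be counted and compared with the planned numbers of exposed participants before the rule is final.

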**Statistical analysis:**

Kaplan-Meier curves will be plotted, and Cox proportional HRs and 95% CIs will be calculated. Stratified analysis will be performed by class of β-blocker, intrinsic sympathomimetic effect and indication(s) for prescription.

**Ethics and dissemination:**

This study was ethically approved by the Independent Scientific Advisory Committee of the Medicines and Healthcare Authority (Ref 18_227R). The results of this study will be published in peer-reviewed journals and presented at conferences.

**Summary:**

This prospective cohort study will evaluate the analgesic potential of commonly used drugs for osteoarthritis pain.

Strengths and limitations of this studyThe study has a large sample size and uses a nationally representative data set.The study accounts for propensity score for β-adrenoreceptor drug prescription.The study compares the results of propensity score matching and adjustment analysis.A limitation is that this is a non-randomised study.Data on drug consumption were unavailable.

## Introduction

Osteoarthritis is the most common form of arthritis worldwide. Its prevalence is increasing due to an ageing population and obesity epidemic.^1 2^ It is a leading cause of disability among older adults, with an estimated lifetime risk of 25% and 45% for hip and knee osteoarthritis, respectively.^3 4^ There is no specific therapy for osteoarthritis, and management focuses on symptomatic treatment, with total joint replacement reserved for those with severe symptomatic disease. However, analgesic and anti-inflammatory drugs only have modest efficacy for osteoarthritis pain, with mean Western Ontario and McMaster Universities Arthritis Index improvement of 3.99–11.24 across a spectrum of non-steroidal anti-inflammatory drugs (NSAIDs) and opioids.^5^ Apart from this, NSAIDs and cyclo-oxygenase II inhibitors increase the risk of gastrointestinal bleeding, acute kidney injury, chronic kidney disease, coronary heart disease, hypertension, stroke and congestive cardiac failure, and are associated with increased cardiovascular mortality.^6–18^ These adverse effects are particularly important for people with osteoarthritis as they already have a high burden of cardiovascular comorbidities and risk factors.^19 20^ Consequently, healthcare practitioners are reluctant to prescribe NSAIDs as these patients are often on antiplatelet therapy for primary prevention or dual antiplatelet therapy following a cardiovascular event, meaning that prescription of NSAIDs would expose patients to unacceptably high bleeding risk, and so the prescription of potent opioids for osteoarthritis pain has increased over the last decade.^21^ However, opioids induce dependence and increase the risk of falls, fractures and death.^22–25^ Thus, there is a need to develop safe, effective, well-tolerated, non-addictive analgesics to target osteoarthritis pain that can be prescribed safely to patients with cardiovascular comorbidities.

We recently demonstrated a negative association between self-reported β-adrenoreceptor blocking drug use and pain severity (adjusted OR (aOR) 0.68; 95% CI 0.51 to 0.91) and use of opioid analgesics (aOR 0.73; 95% CI 0.54 to 0.98) in community-dwelling adults with large-joint lower-limb osteoarthritis.^26^ We also found that each year of treatment with β-adrenoreceptor blocking medicines reduces the risk of joint pain (aOR 0.96; 95%CI 0.93 to 0.99; p<0.004),^26^ and that other classes of antihypertensive medications, including α-adrenoreceptor blocking drugs, did not associate with joint pain or analgesic use.^26^

The purpose of this study is to explore the analgesic potential of β-adrenoreceptor blocking drugs and to identify the drug class that is most likely to have an analgesic effect. The specific objectives are to examine the association between β-adrenoreceptor blocking drug prescription and incident knee osteoarthritis, incident hip osteoarthritis, incident knee pain, incident hip pain, analgesic prescription in knee or hip osteoarthritis, and total knee or hip joint replacement. We hypothesise that patients prescribed β-adrenoreceptor blocking drugs are less likely to develop incident symptomatic lower limb osteoarthritis, and in those who have symptomatic osteoarthritis to associate with fewer analgesic prescriptions and to slow the progression to total joint replacement due to the analgesic effect. Additionally, we will also explore data to identify the class of β-adrenoreceptor blocking drug that is most likely to have an analgesic effect.

## Methods

### Study design

This is a cohort study.

#### Data source

Data from the Clinical Practice Research Datalink (CPRD) will be used in this study. Incepted in 1987, the CPRD is a longitudinal anonymised electronic database containing health records of >10 million people in the UK.^27^ CPRD participants are representative of the UK population in terms of age, sex and ethnicity.^27^ The CPRD contains details of diagnoses and primary care prescriptions. The data are enhanced by linkage with hospitalisation (Hospital Episode Statistics) and mortality records (Office of National Statistics).

### Study population

All CPRD registered participants contributing acceptable quality data in up-to-standard general practices (GP) between 1 January 1990 and 31 December 2017 are included. Two separate cohort studies will be performed.

#### Cohort study 1

Cohort study 1 will be on β-adrenoreceptor blocking drug prescription and incident osteoarthritis. Exposure will be ≥2 continuous prescriptions for β-adrenoreceptor blocking drugs, and will be further categorised according to duration of treatment (≤6 months, 7–12 months, 12–24 months and >24 months). The outcomes will be knee osteoarthritis (primary), hip osteoarthritis, knee pain and hip pain.

##### Inclusion criteria

###### Exposed

≥2 continuous prescriptions of β-adrenoreceptor blocking drugs defined as two consecutive prescriptions ≤60 days apart.Age ≥40 years on the date of the first of the two consecutive β-adrenoreceptor blocking drug prescriptions.

###### Unexposed

Age (5-year age band based on year of birth), sex, GP surgery, year first registered in CPRD (±1 year) and propensity score for β-adrenoreceptor blocking drug prescription matched to the exposed participants.

##### Propensity for β-adrenoreceptor blocking drug prescription

As participants prescribed β-adrenoreceptor blocking drugs are likely to have comorbidities, be older and have a high body mass index (BMI), a propensity score for β-adrenoreceptor blocking drug prescription will be calculated using a cumulative logit regression model and including demographic factors and relevant diagnoses at any time prior to β-adrenoreceptor blocking drug prescription (box 1).

Box 1List of potential variables to be included in the calculation of propensity score for β-adrenoreceptor prescriptionDemographic factors.Body mass index (WHO classification categories)*, smoking status* and deprivation score (general practice-level Index of Multiple Deprivation Score).Comorbidities.Hypertension, angina, myocardial infarction, congestive cardiac failure, atrial fibrillation, stroke, high cholesterol, chronic kidney disease, diabetes, anxiety, migraine, Charlson Comorbidity Index (excluding comorbidities in the propensity score) and duration in years of cardiovascular comorbidities prior to cohort entry.Drug prescriptions.Calcium channel blockers, ACE inhibitors, angiotensin II receptor antagonists, bendroflumethiazide, aldosterone antagonists, loop diuretics, alfa-adrenoreceptor blocking drugs, nitrates, nicorandil, aspirin, clopidogrel, statin, fibrate, vitamin K antagonists and non-steroidal anti-inflammatory drugs (in the progression cohort), and as a marker of severity of underlying disease at cohort entry the number of antihypertensive, antiarrhythmic or antianginal drugs prescribed in the 12-month period prior to cohort entry.*Categorised as missing if not available.

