### Statistical analysis

Covariate balance between matched exposed and unexposed participants will be examined. Unbalanced covariates will be included in the model as separate covariates. Other covariates that do not influence exposure but influence outcomes or reflect health-seeking behaviour alone may be included in the model after evaluating their balance between exposed and unexposed groups. These are the following:

Number of GP consultations in the 12-month period preceding cohort entry.Number of hospital outpatient referrals in the 12-month period preceding cohort entry.Number of hospital admissions in the 12-month period preceding cohort entry.Total number of GP consultations for knee or hip injury prior to cohort entry.Non-osteoporotic fractures, defined as fractures in any bone except the femur, distal radius and vertebrae, after the age of 18 years but before the age of 50 years in women and 60 years in men. This is a surrogate for physically active occupation or lifestyle that may associate with incident osteoarthritis.

Participants will enter the cohort on the index date, and data will be censored at the earliest of an event, study end date (31 December 2017), date of death, transfer out of CPRD for all outcomes, and additionally date of the last prescription of β-adrenoreceptor blocking drugs, plus 4 weeks (usual duration of GP prescription in the UK) for incident osteoarthritis, incident knee or hip pain, or new analgesic prescription. Given the reported effects of propranolol on pain sensitivity in patients with fibromyalgia,^34^ we anticipate β-adrenoreceptor blocking drugs to have an analgesic effect in the short term, and outcome events >4 weeks after the date of the last β-adrenoreceptor blocking drug prescription will not be included in the analysis, except for total joint replacement which may be delayed due to a period of analgesia.

Time to event data in the exposed and unexposed groups will be compared using Kaplan-Meier survival curves. Schoenfeld residuals will be examined to see if survival curves meet the assumptions of the proportional hazard model. Cox proportional HRs and 95% CI will be calculated for each incident outcome using the first Read code for the event. Similarly, HRs will be calculated for new analgesic prescriptions, defined as prescription for NSAIDs, opioids, gabapentin and pregabalin, respectively, in those exposed to β-adrenoreceptor blocking drugs, with unexposed as the referent.

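### BMI enters the propensity score only as WHO bands, which can leave a small within-band BMI difference that a balance check on the same bands would miss

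*Protocol article*

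**What the plan says.** The section on the propensity for β-blocker prescription justifies the score by noting that exposed people are "likely to have comorbidities, be older and have a high body mass index (BMI"). The Introduction says of osteoarthritis: "Its prevalence is increasing due to an ageing population and obesity epidemic". On the protocol's own account, BMI is therefore linked to both exposure and outcome.

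Box 1 gives the form in which BMI enters the score: "Body mass index (WHO classification categories"), with a separate category when it is not recorded. It does not say how many bands are used. Cohort study 2 calculates its score in the same way and adds further variables.

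The direct matching variables are "Age (5-year age band based on year of birth), sex, GP surgery, year first registered in CPRD (±1 year") and the propensity score. BMI is not one of them. Matching on the score is described thus: "Nearest neighbour matching (±0.2 SD) will be used to match exposed to unexposed participants".

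The Statistical analysis section then says: "Covariate balance between matched exposed and unexposed participants will be examined". It continues: "Unbalanced covariates will be included in the model as separate covariates". It does not say whether BMI is compared in bands or in kg/m². BMI is not on that section's list of further outcome-model covariates.

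**The concern.** When one group is heavier on average, its members tend to sit higher inside each BMI band, above all in an open-ended top band. Equal band proportions therefore do not guarantee equal mean BMI. If obesity raises the risk of osteoarthritis, the remaining difference raises the HR for β-blocker exposure.

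The rest of the plan does not clearly remove this. The sensitivity analysis with the score as a covariate reuses the banded score. Multiple imputation addresses missing BMI, not coarsened BMI. The restrictions by indication concern cardiovascular disease. The balance check would help if done in kg/m² but not if done on the bands, and the protocol leaves this open.

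At stake is some attenuation of a true protective association in both primary analyses, knee osteoarthritis and total knee replacement.

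**Working it through.** **1. The plan's own figure.** The documents hold no BMI figure, but the sample size fixes the scale against which a bias can be judged. Inputs from the Sample size section: HR 0.70, one exposed to four unexposed, 80% power, 1% type I error (taken as two-sided), knee osteoarthritis incidence 6.5 per 1000 person-years.

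- Events = (2.576 + 0.842)² / [0.2 × 0.8 × (ln 0.70)²] = 11.679 / (0.16 × 0.12722) = 573.8, so 574.
- Total = 573.8 / 0.0065 = 88 273, as stated (one person-year each).

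**2. Assumptions about BMI (none is in the documents).** Log-normal BMI; unexposed mean 27, SD 5; exposed mean higher by 0.5 to 3 kg/m² with the same SD; osteoarthritis HR of 1.2, 1.35 or 1.5 per 5 kg/m². Bands are cut at 18.5/25/30 (four) or 18.5/25/30/35/40 (six). Band proportions are taken as perfectly balanced, and no other covariate is used.

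**3. Formulas.** The unexposed are reweighted to the exposed band proportions p₁(b).

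- Remaining gap = E₁[BMI] − Σ p₁(b) E₀[BMI | b].
- Null HR = E₁[exp(β·BMI)] / Σ p₁(b) E₀[exp(β·BMI) | b], with β = ln(HR per 5 kg/m²) / 5.

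**4. Results.** HR ranges run over 1.2 to 1.5 per 5 kg/m², with upper ends rounded up.

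| Crude gap (kg/m²) | Six bands: gap left | Null HR | Four bands: gap left | Null HR |
|---|---|---|---|---|
| 0.5 | 0.054 (11%) | 1.002–1.004 | 0.071 (14%) | 1.003–1.006 |
| 1 | 0.103 (10%) | 1.003–1.007 | 0.143 (14%) | 1.005–1.013 |
| 2 | 0.188 (9%) | 1.006–1.012 | 0.297 (15%) | 1.011–1.028 |
| 3 | 0.257 (9%) | 1.008–1.017 | 0.479 (16%) | 1.019–1.047 |

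Hand check for a gap of 1 kg/m² and HR 1.35 per 5 kg/m²: with no BMI control the null HR is 1.35^(1/5) = 1.062. After four bands it is about 1.35^(0.143/5) = 1.009.

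**5. Sensitivity to the assumptions.** A wider grid used normal or log-normal BMI, mean 27 to 28, SD 4.5 to 5.5, gap 0.5 to 2 kg/m² and HR up to 1.6 per 5 kg/m². It leaves 7 to 12% of the gap with six bands (null HR 1.001 to 1.018) and 14 to 20% with four (1.003 to 1.055). The upper end therefore depends on the shape of the BMI distribution, but the order of size does not change.

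**6. Effect on the planned analysis.** Power = Φ(|ln HR| × √(574 × 0.16) − 2.576). A bias factor of 1.01 turns a true 0.70 into 0.707: 0.3467 × 9.583 − 2.576 = 0.747, power 77%. A factor of 1.03 gives 0.721 and power 71%. Both apply only at the minimum of 574 events.

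**The case against.** A reader might infer that the balance check cannot see the remaining difference. The documents do not support that. They do not restrict the check to bands, and if BMI in kg/m² were found unbalanced, the existing rule would already bring it into the model. What stands is conditional: a check on the bands alone would miss it, and the text does not rule that out.

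A reader might also infer that exposed people will certainly stay heavier after matching. That is not established either. The score contains hypertension, diabetes, high cholesterol and many cardiovascular drugs, all plausibly related to BMI, and matching also uses age, sex and practice. These could shrink or enlarge the within-band gap, so balance on BMI bands alone is not the planned analysis.

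The other counterarguments are fair. The bias is small against the planned HR of 0.70 and runs against the protective hypothesis. More events than the minimum would restore power, although they would not remove the bias. Box 1 lists candidate variables, and the limitations section acknowledges residual confounding. But the form of BMI is stated rather than left open, and a general caveat is no reason to keep a component that can be reduced at no cost. A claim that banding costs precision in the outcome model would not hold: BMI enters that model only if unbalanced.

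**Conclusion.** The point holds as a minor, free improvement. An expected confounder is written into the score in coarsened form, and the plan does not ensure that a within-band difference would be noticed. Under the assumptions in the working, about 9 to 16% of the BMI gap remains, and a null HR reads about 1.002 to 1.017 (six bands) or 1.003 to 1.047 (four bands). The number of bands matters and is not given. The assumed direction is upwards, so this could dilute a protective association but could not produce one. All sizes rest on assumed BMI values and on balancing BMI bands alone; correlated covariates could move the result either way. The sample size calculation is unaffected.

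**What to change.** In Box 1, and hence in both propensity scores, replace the BMI categories by the last recorded BMI before the index date as a continuous term, for example a restricted cubic spline, with an indicator for not recorded. In the Statistical analysis section, state that BMI balance is checked in kg/m² among those with a record, and that continuous BMI is added to the Cox model if it is unbalanced.

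The continuous term in the score does most of the work. The largest gap in the table is 0.479 / 5 = 0.096 SD, which a kg/m² check with a threshold of 0.1 (an assumption; the protocol states none) would pass. Putting BMI into the two primary Cox models whatever the balance is optional.

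The cost is analysis wording only: forming the bands already requires the measured values.
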